### Instruments

#### Primary outcome

##### Depressive symptoms

Symptoms of depression will be assessed with the Center for Epidemiological Studies Depression Scale (CES-D) [31,38]. It measures the frequency of 20 depressive symptoms over the past week using 4-point Likert scales. The total score range is 0 to 60, with a higher rating meaning more depressive symptoms. Computerised and paper-and-pencil versions of the CES-D correlate at a very high level [39]. The web-based CES-D has proved a reliable and valid screening instrument in a Dutch adolescent population [32].

#### Secondary outcomes

##### Anxiety symptoms

The anxiety subscale of the Hospital Anxiety and Depression Scale (HADS) [40] will be used to assess anxiety symptoms. The Dutch version of the HADS has been validated [41]. The anxiety subscale consists of seven items measuring anxiety symptoms on a 4-point Likert scale, with a score range of 0 to 21, and a higher rating indicating a higher state of anxiety.

#### Perceived control

The Dutch version of the 5-item Mastery Scale will be used to assess perceived control [42]. The concept of mastery refers to beliefs about one's own ability to control one's environment. Responses are rated on a 5-point Likert scale, with a total score range of 5 to 25; a higher score indicates a greater sense of mastery. The Mastery Scale has good psychometric properties [42].

#### Additional measures

##### Motivation

At baseline we will assess motivation to take part in preventive group interventions, using four subscales of the Nijmegen Motivation List for Prevention (NML-P) [43]. The subscales are Readiness, Doubt, Support and Burden. Their reliability is acceptable, with Cronbach's alphas ranging from .80 to .84.

#### Other information

At baseline we will also assess demographic information and any previous or present receipt of professional help for psychological problems. Follow-up assessments will record the use of professional help (t1 and t2) and participants' evaluations of the intervention (t1, in course group only).

Course adherence will be measured in terms of session attendance and completion of homework assignments. Session attendance will automatically be recorded when the participant enters the chatroom. Homework completion will be recorded by the facilitators in an online logbook.

### Sample size

The trial is powered to detect a clinical effect size of *d *= 0.32 or larger in a one-sided test (alpha = .05) at a power of 80% (1-β). The hypothesis is directional, with better outcomes expected for the course group. A total of 242 participants are needed in the study, n = 121 per condition.

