**Methods:**

We will conduct a randomised controlled trial (RCT) in which 244 young people aged 16-25 are randomly allocated to the Grip op Je Dip (GOJD) online group course or to a waiting list control group. The participants will be recruited from the general population. The primary outcome measure will be the severity of depressive symptoms according to the Center for Epidemiological Studies Depression Scale (CES-D). Other outcomes will include anxiety (Hospital Anxiety and Depression Scale-Anxiety, HADS) and mastery (Mastery Scale). Assessments will take place in both groups at baseline and three months later. Effect maintenance will be studied in the GOJD group six months after baseline, with missing data imputed using the expectation-maximisation method. Mediators and predictors of better outcomes will also be identified.

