The current study will focus on one specific type of Internet-based intervention: a professionally facilitated, cognitive-behavioural group course designed for young people with symptoms of depression. The perceived advantages of online group sessions as compared to individual approaches are social support and mutual recognition by group members (though they remain anonymous to one another) and the reduction of professional contact hours per participant as compared to individual treatment with support [25]. Three earlier studies on online group courses in mental health care have found positive outcomes in pre-post measurements, although relatively high attrition rates were reported, a general problem in Internet interventions [26].

Despite the clear benefits of web-based interventions for depression and their availability for all age groups from about 13 onwards, there is a lack of outcome studies on adolescents [27,28]. Only two randomised controlled trials have been conducted on prevention programmes for depression and anxiety [29,30]. The Calear study found that a universal prevention programme was effective in reducing symptoms of anxiety and depression only in males. The Van Voorhees study showed that a web-based behavioural change programme in primary care, in combination with either motivational interviewing or brief advice, was associated with declines in depressed mood and in the likelihood of clinical depression symptom levels; in combination with motivational interviewing it reduced the likelihood of depressive episodes and hopelessness.

The primary aim of the study we describe here will be to evaluate the effectiveness of a web-based group course called Grip op Je Dip (Master Your Mood), designed for young people aged 16 to 25 with depressive symptoms, by comparing it to a waitlisted control group. Secondary aims concern effect maintenance and potential predictors of positive outcomes. The present article describes and discusses the study design.

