### Sample

The sample is to consist of 242 young people aged 16-25 with mild to moderate depressive symptoms. The inclusion criteria are as follow: age 16 to 25, informed consent (including parental consent if aged 16 or 17) and a CES-D depression score from 10 to 45. The CES-D cut-off score for clinical depression is 16 [31] for adults, and for adolescents it is either 22 [32] or 24 [33]. For subclinical depression, no CES-D cut-off scores have been determined, but we have set the lower limit at 10 for this study. Applicants will be excluded if there are indications of suicidal ideation with intent and plan as assessed with the MINI-International Neuropsychiatric Interview (MINI-Plus) [34,35]. MINI-Plus assessment is mandatory for individuals with CES-D scores higher than 24; the MINI-Plus will be administered online in the chatroom.

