### Conditions: the intervention

The GOJD online course derives from the face-to-face intervention of the same name developed by the Trimbos Institute (Netherlands Institute for Mental Health and Addiction). That intervention was based on the Dutch version of the Coping with Depression Course [36]. The face-to-face course was adapted to the Internet in a collaborative effort involving the Trimbos Institute and three mental health institutions [37].

The resulting online GOJD group course is a structured, psychoeducational form of cognitive-behavioural therapy for depression. The core focus is the cognitive restructuring of thinking patterns. Course participants are encouraged to detect their own unproductive, unrealistic thoughts, and they are then taught to transform these into realistic, helpful thoughts. Performance of pleasant daily activities is also encouraged, and a mood measure is filled in daily to help understand the connection between pleasant activities and mood level. The course is given in a secured chatroom that is part of the website http://www.gripopjedip.nl, which also provides information and video films about depression. Participants' anonymity is guaranteed by a self-chosen nickname. Only a mobile phone number must be given to facilitators for sending pre-session SMS reminders. The course makes use of text and figures, smileys to express feelings in written texts, and home exercises.

GOJD consists of six 90-minute sessions, conducted at a fixed time once a week. The course is facilitated by one or two trained mental health promotion workers, depending on group size (a maximum of 6) and their experience in conducting online courses. Facilitators receive two days' prior training in the technical and therapeutic conduct of the course and in administering the online MINI-Plus interview.

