### Statistical analyses

To assess whether the randomisation results in two comparable groups at baseline, and whether differential loss to follow-up later occurs, we will use t-tests, chi-square tests and logistic regression (p < .10). Analyses with regard to effectiveness will be based on the intention-to-treat principle.

Missing data at t1 and t2 will be imputed using the expectation-maximisation (EM) method, as implemented in SPSS Missing Value Analysis. It imputes missing values by maximum likelihood estimation using the observed data in an iterative process [44]. All randomised participants will be included in the analyses in line with their allocation, regardless of how many sessions they complete (intention-to-treat principle).

Since the online GOJD is a group course, some subjects will be participating in the same course group, leading to some amount of clustering. The clustering would violate the assumption of independence of observations and might thus affect standard errors and *P*-values. We will therefore use linear regression models, controlling for data clustering, in analysing post-test (t1) between-group differences on the continuous outcome measures. Robust standard errors and correct *P-*values will be obtained using the first-order Taylor-series linearisation method, as implemented in Stata.

Magnitudes of intervention effects will be estimated using Cohen's *d *[45]. Effect sizes will first be calculated for each condition separately by subtracting the mean post-test score from the mean pre-test score and dividing the result by the standard deviation at pre-test. The effect size of the comparison group will then be subtracted from that of the experimental group. A difference in *d *0.5 would indicate that the experimental group mean is half a standard deviation greater than the control group mean. For Cohen's *d*, an effect size of 0.2 to 0.3 may be regarded as a small effect, around 0.5 as a medium effect and 0.8 to infinity as a large effect.

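### The 80% power stated for 242 participants makes no allowance for course-group clustering or missing three-month data, so any of either takes the comparison as written below 80%

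*Protocol article*

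**What the plan says.** The Sample size section takes d = 0.32 as the smallest effect to be detected, with a directional test at alpha .05 and 80% power. It concludes: "A total of 242 participants are needed in the study, n = 121 per condition". It mentions neither clustering nor missing data. The Sample section sets recruitment at the same number ("The sample is to consist of 242 young people aged 16-25 with mild to moderate depressive symptoms"), so there is no recruitment margin. The Methods paragraph of the abstract gives a different target: "244 young people aged 16-25 are randomly allocated".

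Other sections raise both of the omitted features:

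- **Clustering.** The Statistical analyses section says that "some subjects will be participating in the same course group, leading to some amount of clustering". It adds that this breaks the independence assumption and may affect standard errors, and it plans cluster-robust standard errors for the t1 comparison. Under Conditions: the intervention, six is given as the upper limit on group size, not as the mean.
- **Missing data.** The Background reports that three earlier studies of online group courses had positive outcomes, "although relatively high attrition rates were reported, a general problem in Internet interventions". The Statistical analyses section plans expectation-maximisation (EM) imputation at t1 and t2. No loss rate is forecast for this trial.

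**The concern.** The power statement assumes independent participants who all supply a t1 score. The analysis section of the same article rejects the first assumption and plans for failure of the second. Since 242 is both the number required and the number to be recruited, nothing absorbs either departure.

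At stake is how the result is read. If the trial finds no clear difference, a reader told that it had 80% power for d = 0.32 may take the result as stronger evidence against an effect of that size than the design can give. The test, its type I error rate and the analysis set are not affected.

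**Working it through.** **Inputs from the article:** d = 0.32 (SD = 1), one-sided alpha = .05, power 80%, 121 per arm, 1:1 allocation, course groups of at most 6, waiting-list arm not grouped.

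**Assumed, because the article gives no value:** ICC 0.02 to 0.10; mean group size m of 4 to 6; t1 loss a of 10% to 40%, equal in both arms.

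**1. Reproduce the plan's figure.** n per arm = 2(1.645 + 0.842)² / 0.32² = 120.75, rounded up to 121, so 242 in total. By the noncentral t, power is 79.9% at 121 per arm and 80.2% at 122 per arm (244 in total). The match with the unadjusted formula shows that no design effect or loss allowance is included. Losing one participant per arm leaves 120, already below 120.75.

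**2. Formula with clustering and loss.** Analysable n = 121(1 − a) per arm and observed group size m(1 − a). Course-arm design effect DE = 1 + [m(1 − a) − 1] × ICC. Only one arm is grouped, so the variance of the difference is inflated by (1 + DE)/2. Power comes from the noncentral t with noncentrality 0.32 / √[2 × (1 + DE)/2 / n].

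Example with ICC 0.05, m = 6, a = 30%: n = 121 × 0.70 = 84.7; group size 4.2; DE = 1 + 3.2 × 0.05 = 1.16; inflation 1.08; noncentrality 0.32 / √(2 × 1.08 / 84.7) = 2.00. Power is 64% and detectable d is 0.40.

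**3. Clustering alone (no loss).**

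| ICC | m = 4 | m = 6 |
|---|---|---|
| 0.02 | 78.8% | 78.2% |
| 0.05 | 77.3% | 75.7% |
| 0.10 | 74.8% | 71.7% |

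**4. t1 loss alone (no clustering).**

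| Loss | Power |
|---|---|
| 10% | 76% |
| 20% | 72% |
| 30% | 67% |
| 40% | 61% |

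**5. Both together.** The most favourable corner (10% loss, ICC 0.02, m = 4) gives 75% power and detectable d 0.34. The least favourable (40% loss, ICC 0.10, m = 6) gives 56% and 0.44.

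**6. Possible offset.** If the t1 model adjusts for baseline CES-D with baseline-outcome correlation r, the variance is multiplied by 1 − r². With ICC 0.05, m = 6 and 20% loss, power is 68% unadjusted, about 79% for r = 0.5 and about 84% for r = 0.6. With 40% loss it is about 69% and 75%. The values of r are also assumptions.

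**7. Imputation.** The loss figures count only participants with an observed t1 score. EM imputation returns the file to 242 rows, but it can recover only what the observed variables predict about the missing scores. Analysing imputed values as if observed makes standard errors too small; it does not restore power.

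**The case against.** Five points can be made for the plan.

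- **The arithmetic is right for its inputs.** This stands. The defect is an omission that conflicts with other sections, not a miscalculation.
- **No attrition rate is forecast.** This stands. The Background speaks of earlier courses and of the field, and does not say whether the attrition was from course sessions or from questionnaires. Only missing questionnaires reduce the analysable number, and the Assessments section plans reminders and payments of up to 25 euros to limit them. A reader might infer that the article expects high loss at t1 here; it does not say so.
- **Clustering costs little.** This largely stands. With ICC 0.02 to 0.05 and groups of 4 to 6 the cost is about 1 to 4 points. Six is a maximum, so using it as the mean overstates the effect.
- **Baseline adjustment could make up the difference.** This partly stands. Randomisation is stratified by baseline CES-D, and an article may leave the covariate list to a fuller document. But the analysis section names no baseline covariate for the t1 model and the sample-size section does not rely on one, so the offset cannot be credited to the stated 80%. At 40% loss, a correlation of 0.6 would not restore it.
- **A null result would be read from its confidence interval.** This is fair, and the article does plan 95% intervals. It lessens the consequence but does not make the power statement correct.

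**Conclusion.** The point holds in direction, and its size is conditional. For the comparison as written, 80% is the power with independent participants and complete t1 data. Any t1 loss or positive ICC takes it lower. Over the assumed ranges in the working, power is about 75% to 56% with both features present, and loss matters more than clustering over most of those ranges.

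A reader might go further and conclude that the trial is shown to be seriously underpowered, with a definite figure well below 80%. The article does not support that. It gives no ICC, mean group size or t1 loss rate, and a baseline-adjusted analysis with a strong enough correlation could reach 80% under moderate loss.

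The 244 against 242 is a separate inconsistency. It changes power from 80.2% to 79.9% and adds nothing to the argument above.

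**What to change.** Keep the sample and rewrite the sample-size paragraph:

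1. State the assumed ICC, mean course-group size and t1 loss, each with its basis.
2. Give power at d = 0.32 and the detectable d for the number randomised under those assumptions, with variance inflation (1 + [1 + (m − 1) × ICC])/2 because only the course arm is grouped. Show a short range if the inputs are uncertain.
3. Count a gain from baseline CES-D only if the t1 model names it as a covariate, and state the correlation assumed.
4. Use a single target, 242 or 244, in the abstract, the Sample section and the Sample size section.

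The cost is one rewritten paragraph and probably a less favourable stated power. No extra participants are needed, and the randomisation and the primary test stay as they are, unless the baseline covariate is added.

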### Statistical analyses

To assess whether the randomisation results in two comparable groups at baseline, and whether differential loss to follow-up later occurs, we will use t-tests, chi-square tests and logistic regression (p < .10). Analyses with regard to effectiveness will be based on the intention-to-treat principle.

Missing data at t1 and t2 will be imputed using the expectation-maximisation (EM) method, as implemented in SPSS Missing Value Analysis. It imputes missing values by maximum likelihood estimation using the observed data in an iterative process [44]. All randomised participants will be included in the analyses in line with their allocation, regardless of how many sessions they complete (intention-to-treat principle).

Since the online GOJD is a group course, some subjects will be participating in the same course group, leading to some amount of clustering. The clustering would violate the assumption of independence of observations and might thus affect standard errors and *P*-values. We will therefore use linear regression models, controlling for data clustering, in analysing post-test (t1) between-group differences on the continuous outcome measures. Robust standard errors and correct *P-*values will be obtained using the first-order Taylor-series linearisation method, as implemented in Stata.

Magnitudes of intervention effects will be estimated using Cohen's *d *[45]. Effect sizes will first be calculated for each condition separately by subtracting the mean post-test score from the mean pre-test score and dividing the result by the standard deviation at pre-test. The effect size of the comparison group will then be subtracted from that of the experimental group. A difference in *d *0.5 would indicate that the experimental group mean is half a standard deviation greater than the control group mean. For Cohen's *d*, an effect size of 0.2 to 0.3 may be regarded as a small effect, around 0.5 as a medium effect and 0.8 to infinity as a large effect.

To determine effect maintenance at 6 months in the experimental group, we will use the follow-up (t2) assessment data. The number of participants showing reliable, clinically significant change on the CES-D from pre-intervention to post-intervention and follow-up will be calculated using the method of Jacobson and Truax [46]. To find predictors for more or less successful intervention outcomes, we will use regression analyses to study effect modification. The individual standardised change scores (effectsizes; pre- to post-intervention) will serve as the outcome measure, and interaction terms between the treatment dummy and participants' characteristics will be included as predictors, along with their constituent main effects. Predictors for successful and unsuccessful outcomes will be demographic variables such as age, gender and educational attainment and course-related variables such as web-chatting experience and motivation to take part in preventive group interventions [43].

To detect possible dose-response relationships in respondents randomised to the course, we will use a linear model to regress the primary outcome (depressive symptoms) on the number of sessions they attended. Tests will be conducted at alpha = .05 with 95% confidence intervals.

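### Single EM imputation ignores imputation uncertainty, so intervals are too narrow or mis-centred; false positives rise if trial arm is in the EM model, and the effect shrinks if arms are pooled

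*Protocol article*

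**What the plan says.** In the protocol article, Statistical analyses fixes the method and the software: "Missing data at t1 and t2 will be imputed using the expectation-maximisation (EM) method, as implemented in SPSS Missing Value Analysis". It describes the method in one sentence: "It imputes missing values by maximum likelihood estimation using the observed data in an iterative process". The Abstract names the same method: "with missing data imputed using the expectation-maximisation method".

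The completed data are then used in full: "All randomised participants will be included in the analyses in line with their allocation, regardless of how many sessions they complete (intention-to-treat principle"). The between-group model follows: "We will therefore use linear regression models, controlling for data clustering, in analysing post-test (t1) between-group differences on the continuous outcome measures". The reason given for robust inference is that members of one course group are not independent. On the standard errors and P-values, which the article describes as robust and correct, the text reads: "values will be obtained using the first-order Taylor-series linearisation method, as implemented in Stata".

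The article describes no repeated imputation, pooling, bootstrap or sensitivity analysis for missing data. It gives no expected rate of missing questionnaires. The Background says of earlier online group courses that results were positive, "although relatively high attrition rates were reported, a general problem in Internet interventions".

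**The concern.** A score imputed once and then analysed as if observed contributes to the sample size but brings no information beyond what the observed data already held. The standard error must allow for this, and here it cannot. Taylor linearisation works from the residuals of the completed data set. It corrects for correlation within course groups, but it cannot tell an imputed score from a measured one. If the imputed score is a predicted mean, its residual is close to zero, and the residual variance is understated as well.

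The primary comparison at t1 is at stake. If imputation respects arm, the test is too liberal and the interval too narrow. If it ignores arm, the missing scores carry no treatment difference and the estimate is pulled towards zero. The reliable-change counts on the CES-D at t1 and t2 also rest on the imputed scores, and a single imputed value for a non-responder says little about whether that person changed reliably.

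**Working it through.** **1. The plan's own figure.** Sample size gives d = "0.32 or larger in a one-sided test (alpha = .05"), power 80%, 121 per arm. Check: n per arm = 2(1.645 + 0.842)² / 0.32² = 12.37 / 0.1024 = 120.8, so 121 per arm and 242 in total. This is the number needed with complete data.

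**2. Arm in the EM model, baseline-adjusted analysis.** Let a share m of t1 scores be missing completely at random, let σ² be the residual variance, and let each missing score be replaced by its predicted mean.
- True variance of an arm mean: σ² / [n(1−m)], because only the observed scores inform it.
- Reported variance: the residual sum of squares comes from the n(1−m) observed scores but is treated as n scores, giving n(1−m)σ² / n² = (1−m)σ² / n.
- Reported SE / true SE = √[(1−m)²] = 1−m.
- Actual one-sided type I error = 1 − Φ(1.645(1−m)). At m = 0.20 this is 1 − Φ(1.316) = 9.4%.

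Simulation used 121 per arm, robust standard errors and no clustering. The r = 0.5 column runs from analysis without to analysis with baseline adjustment. The r = 0.3 and 0.6 column (3,000 runs per setting) gives the range over both correlations and both analyses.

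| Missing | Formula | Simulated, r = 0.5 | Simulated, r = 0.3 and 0.6 | 95% CI coverage, baseline-adjusted (r = 0.3 and 0.6) |
|---|---|---|---|---|
| 5% | 5.9% | about 5.5% | not run | not run |
| 10% | 6.9% | 6-7% | 6.0-7.6% | about 93% |
| 20% | 9.4% | 8-10% | 7.8-10.1% | about 88% |
| 30% | 12.5% | 10-13% | 9.3-12.9% | about 83% |
| 40% | 16.2% | 14-17% | 11.2-16.6% | about 76% |

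The simulated ratio of reported to true SE with baseline adjustment was about 0.90, 0.80, 0.69 and 0.60 at 10% to 40% missing, as the formula predicts. The estimate itself was not biased: a true 0.32 was recovered as 0.32 throughout. In this variant the fault lies in the error bars.

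**3. A random residual added to each imputed score, still one data set.** Type I error at r = 0.5 was 8.8% at 20% missing and 10.1% at 30%. Over r = 0.3 and 0.6 it was 7.5-8.7% and 9.0-10.6%.

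**4. Arms pooled in the EM model.** Imputed scores carry no arm difference, so the expected estimate is (1−m) × 0.32 = 0.256, 0.224 and 0.192 at 20%, 30% and 40% missing. Simulation gave 0.26, 0.22 and 0.19. Type I error stayed at 4.4-5.7%. Coverage for a true 0.32 was 90%, 82% and 68% with baseline adjustment.

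Power without baseline adjustment was about 71%, 63% and 55%, against the planned 80%. Much of that loss comes from the missing data themselves: by Φ(0.32√[121(1−m)/2] − 1.645), the observed participants alone give 72%, 67% and 61%. With baseline adjustment, power equalled that of the observed-data analysis, so there pooling damages the estimate and interval rather than the power.

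**5. Alternatives.** Regression on the observed scores alone rejected 4.2-5.9% under the null for 10% to 50% missing. Multiple imputation with Rubin's rules gave about 5%, with 94-95% coverage.

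**The case against.** Five points can be made for the plan.

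- **Type I error is not inflated in every version.** With arms pooled in EM it is held. A reader might infer that P-values are always too small, or that a significant primary result would be an artefact of imputation. The article does not support that, because it does not say whether arm is in the EM model; in the pooled version the error runs towards the null. This stands, and it limits what can be claimed.
- **The list of EM variables is detail.** A journal article may leave it to the full protocol or analysis plan, so its absence is no fault in itself. This stands. The list matters here only because it decides which of the two consequences follows.
- **How the software fills in values is assumed.** The article does not say whether a residual is added. This stands for the exact figures, but inflation remains when a residual is added to a single data set.
- **Missing data may be few.** The Background gives no rate and does not say whether attrition means leaving the course or not returning questionnaires; only the latter matters here. Assessments plans reminders at five and ten days and up to 25 euros for completing both follow-ups. This stands: at 5-10% missing the distortion is modest.
- **No t2 test is named.** A reader might infer an overconfident maintenance test. The text names only the use of t2 data and reliable-change counts, so the point there is limited to counts that depend on imputed scores.

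None of these supplies the missing step. The article fixes a single imputation followed by an analysis that ignores it.

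**Conclusion.** The concern holds in a conditional form. Imputation uncertainty is never carried into the analysis, and the clustering correction does not supply it, so valid P-values and 95% intervals are not obtained under either version of the EM model. With arm in the model, false positives rise from the nominal 5% to about 8-10% at 20% missing and 10-13% at 30%. With arms pooled, false positives are held but the effect shrinks in proportion to the share missing. The direction of the error therefore cannot be stated from the article alone.

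The figures assume missingness completely at random, no clustering, the missing rates shown and, apart from step 3, conditional-mean imputation. The main figures take r = 0.5. Informative dropout was not examined. Because the primary test is affected and the method is stated rather than left open, the text should be changed before the data are analysed.

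**What to change.** Replace single EM imputation with multiple imputation in Stata, which the plan already uses for the regression. Impute by arm or with arm in the model, using baseline CES-D, HADS anxiety, mastery and the two stratification factors. Run the planned cluster-robust regression in each imputed data set and combine the results by Rubin's rules. A likelihood model on the observed scores is an acceptable alternative if it also accounts for course-group clustering. Derive the reliable-change counts at t1 and t2 from the same imputations.

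The cost is a few sentences of analysis text and a few lines of code; no further data are needed. Intervals become somewhat wider and correct. The loss of information also becomes visible: by the power formula above, without baseline adjustment, power for d = 0.32 is about 76%, 72%, 67% and 61% at 10%, 20%, 30% and 40% missing.

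### Single EM imputation of missing t1 scores makes the primary test and intervals unreliable: false positives rise if the EM model uses allocation, and the effect is diluted if it does not

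*Protocol article*

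**What the plan says.** All the relevant steps are in the protocol article, Methods, Statistical analyses.

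- **Missing data:** "Missing data at t1 and t2 will be imputed using the expectation-maximisation (EM) method, as implemented in SPSS Missing Value Analysis". The method is described further: "It imputes missing values by maximum likelihood estimation using the observed data in an iterative process". The abstract also names EM imputation.
- **Analysis set:** "All randomised participants will be included in the analyses in line with their allocation, regardless of how many sessions they complete".
- **Model:** "linear regression models, controlling for data clustering, in analysing post-test (t1) between-group differences on the continuous outcome measures".
- **Standard error:** robust standard errors and P-values, which the article describes as correct, "will be obtained using the first-order Taylor-series linearisation method, as implemented in Stata". The reason given is that participants share course groups.

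The article mentions no repeated imputation, no pooling of variances and no other allowance for imputation. It does not say which variables enter the EM model, whether allocation is one of them, or whether EM is run separately by arm. It gives no expected loss at t1. The Background says of earlier online group courses that results were positive, "although relatively high attrition rates were reported, a general problem in Internet interventions".

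**The concern.** The regression receives one completed data set. Nothing in it marks which t1 scores were measured and which were predicted. The linearised standard error allows for correlation within course groups, which is a different problem. The analysis therefore works with 242 outcomes when fewer were observed.

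This is the main test of the course on CES-D, and the same model serves anxiety and mastery. At stake are the 5% error rate, the 95% intervals and the size of the reported effect. The method, analysis set, model and variance estimator are all stated. The point therefore concerns a choice that has been made, not a detail left to a fuller document.

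**Working it through.** **Inputs from the article.** d = 0.32, one-sided alpha .05, power 80%, 121 per condition (Sample size).

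**Assumptions.** Fraction f of t1 scores missing, 10% to 40%, completely at random and equal in both arms; t0-t1 correlation r = 0.5; EM predicts t1 from baseline CES-D; t1 comparison not adjusted for baseline; no clustering unless stated.

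**The plan's own figure.** n per arm = 2(1.645 + 0.842)²/0.32² = 120.8, so 121 per arm and 242 in total. Power at 121 per arm is 80.1%. The sample size reproduces.

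**Case A: EM includes allocation or is run by arm.** In units of the complete-data variance:

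- variance the regression reports: (1 − f) + f·r²
- actual variance of the estimate: (1 − r²)/(1 − f) + r²
- one-sided error: 1 − Φ(1.645 × SE ratio)
- 95% coverage: 2Φ(1.96 × SE ratio) − 1

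For f = 0.3 the reported factor is 0.7 + 0.075 = 0.775 and the actual factor is 0.75/0.7 + 0.25 = 1.321. The SE ratio is √(0.775/1.321) = 0.766.

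| Missing | Reported factor | Actual factor | SE ratio | One-sided error | Coverage |
|---|---|---|---|---|---|
| 10% | 0.925 | 1.083 | 0.924 | 6.4% | 93% |
| 20% | 0.850 | 1.188 | 0.846 | 8.2% | 90% |
| 30% | 0.775 | 1.321 | 0.766 | 10.4% | 87% |
| 40% | 0.700 | 1.500 | 0.683 | 13.1% | 82% |

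Simulation gives one-sided error of 6.4%, 8.2%, 10.7% and 13.8%. At 30% missing the reported SE is 0.113 and the true SD is 0.148. The estimate is unbiased.

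Variations on Case A:

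- **Baseline-adjusted regression:** the SE ratio is 1 − f, so one-sided error is 6.9%, 9.4%, 12.5% and 16.2%.
- **A single random residual added to each imputed value** (baseline-adjusted): still about 10.5% at 30% missing.
- **Clustering** (ICC 0.05, groups of 6, 30% missing): 10.4% unadjusted and about 13% adjusted. The cluster-robust SE does not repair the error.

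**Case B: one pooled EM without allocation.** Imputed scores carry no treatment difference, so the expected estimate is 0.32(1 − f). The reported SE is √(2/121) = 0.1286 times the square root of the reported factor above. It is close to the estimator's actual spread: in simulation at 30% missing, 0.112 against 0.113.

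- power: Φ(0.32(1 − f)/SE − 1.645)
- coverage, with b = 0.32f/SE: Φ(1.96 − b) − Φ(−1.96 − b)

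For f = 0.3, SE = 0.1286 × √0.775 = 0.1132. Power is Φ(0.224/0.1132 − 1.645) = 63%. With b = 0.096/0.1132 = 0.848, coverage is 86%.

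| Missing | Mean estimate | One-sided power | Coverage |
|---|---|---|---|
| 20% | 0.256 | 70% | 92% |
| 30% | 0.224 | 63% | 86% |
| 40% | 0.192 | 56% | 78% |

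Simulation gives estimates of 0.26, 0.22 and 0.19, power of 70%, 62% and 55%, and coverage of 91%, 86% and 77%. The null one-sided error is 4.8% to 5.5%, or 5.3% to 6.5% with ICC 0.05.

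Not all of the fall from 80% is due to the imputation. A valid analysis with the actual variance of Case A (SE 0.140, 0.148 and 0.157) has power Φ(0.32/SE − 1.645), about 74%, 70% and 65%. The remaining loss in Case B comes from dilution.

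**Check on the remedy.** A baseline-adjusted regression on the observed scores only, used as a stand-in for the proposed methods, gives one-sided error of 4.8% to 5.2% across 10% to 40% missing. At 30% missing its reported SE is 0.132 against a true SD of 0.133.

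**The case against.** A reader might infer that the plan will declare the course effective too often whenever t1 scores are missing, whatever the EM model contains, and that the error favours the course. The article does not support this. A pooled EM without allocation fits the text equally well; under it the false-positive rate stays near 5% and the course is found effective too rarely. Even in Case A the estimate is not shifted. The short standard error inflates both tails equally, and it helps the course only through the one-sided test.

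A reader might also infer that the trial expects heavy loss. The Background speaks of earlier studies and of Internet interventions in general. It gives no questionnaire loss for this trial, and the Assessments section plans reminders at five and ten days and payments of up to 25 euros. The rows for 30% and 40% are assumptions. At 10% missing the one-sided error in Case A is only 6-7%.

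Two smaller objections also stand. That EM adds no random residual is inferred from the description, although adding one does not remove the Case A error. The EM variable list may properly sit in a fuller document.

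The objections do not reach the central point: one completed data set is analysed as if observed, and the standard error named in the article is not designed to account for that.

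**Conclusion.** The concern holds in this form: with t1 scores missing, the stated procedure does not secure the correct P-values it claims, nor valid 95% intervals. With allocation in the EM model, the standard error is too small. Without it, the null error rate is kept, but a real effect is diluted and the intervals are centred in the wrong place.

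The existence of the fault follows from the text. Its direction depends on an EM model that the article does not specify, and its size on a loss rate that it does not give. The figures rest on loss completely at random, equal in both arms, and a correlation of 0.5. With correlations of 0.3 to 0.7, Case A one-sided error at 30% missing ranged from about 9% to 12% unadjusted and stayed near 13% adjusted. With very few missing scores the effect is small. The point still needs correcting because it touches the primary test and is cheap to put right.

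**What to change.** Replace single EM imputation as the basis of all tests and intervals with one of these:

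- **Multiple imputation** that includes allocation, or is run by arm, together with baseline scores. Fit the cluster-corrected regression in each completed set and combine the results by Rubin's rules.
- **A likelihood-based mixed model** of the observed t0 and t1 scores, with an allowance for course-group clustering.

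Both keep everyone as randomised and rest on a missing-at-random assumption. State the variables used for imputation, allocation included. The number of imputations and the covariate list are for the sponsor's statistician.

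The cost is a change of wording in the analysis section and a little more analysis work. Intervals may become wider and P-values less favourable.
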